### Radiograph Interpretation

All recorded radiographs (OPG, IOPAR, and CBCT) will be assessed by 2 investigators. Both the investigators are trained professionals in the field of prosthodontics and oral and maxillofacial surgery, respectively, and have experience of more than 15 years in patient rehabilitation. Before beginning the study, both investigators will be trained in interpreting CBCTs of previously recorded cases that are not related to the current study to practice consistent reading. Each investigator will reassess the recorded radiographs after 1 month to determine intraobserver variability. The findings of the 2 investigators will also be subjected to evaluation of interobserver variability.

## Results

IBM SPSS version 23 and R 4.0.3 will be used for statistical analysis. Results will be aimed at determining the clinical and radiographic success of dental implants in patients with a nonsyndromic alveolar cleft. The Cox model of analysis will be used to determine the shared frailty of dental implants in case of bilateral cleft cases. The Kolmogrov-Smirnov test will be applied to determine the normality of the data. Depending on the data distribution, *t* tests, Wilcoxon tests, and chi-square tests will be utilized to determine statistical significance of clinical and radiological parameters assessed at 3 months and 9 months post implant placement. Binary logistic analysis will be done to compute the predictors of the outcome. CBCTs recorded after dental implant placement will be quantitatively compared to determine the presence of any significant variation in the marginal bone levels. Qualitative assessments of the radiographs will be done to determine the presence of periapical pathology and any other abnormal radiographic findings. Intra- and inter-observer variability in radiographic assessments will be evaluated by using the Kappa statistic. Statistical significance will be set at *P*<.05.

Implant success will be defined based on the guidelines given by Misch et al [19] in the Pisa, Italy Consensus and as presented in the patient record sheet. Statistical comments on the implant survival rate will be given by calculation of a life table analysis.

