### Sample Size Calculation

A recent study showed a success rate of 95% for dental implant–based treatment in cleft patients [10]. With a type I error of 5%, confidence interval of 95%, and 8% margin of error, a sample size of 28 dental implants was obtained. Considering 5% loss to follow-up, an additional 2 dental implants will be placed. Thus, a total sample size of 30 dental implants in sequential patients will be considered for the proposed study.

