### Inclusion Criteria

To be included in the study, patients will need to be older than 16 years, have an asyndromic orofacial cleft, have a unilateral or bilateral cleft alveolus, have undergone secondary alveolar bone grafting (SABG) between 9 and 12 years of age, require single tooth replacement of the lateral incisor/canine region only on the affected cleft side, not have any systemic diseases, and have no symptoms of COVID-19 or tested negative for SARS-CoV-19 virus.

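### The plan does not settle whether a bilateral patient may contribute two implants; if so, only the Cox model allows for within-patient correlation, and the intervals for success and survival would be somewhat too narrow

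*Protocol article*

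**What the plan says.** The unit of the trial is the implant. Sample Size Calculation ends with "a total sample size of 30 dental implants in sequential patients", and Patient Selection continues recruitment until that number of implants is reached. No number of patients is given.

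Inclusion Criteria accept unilateral and bilateral cleft alveolus, with no cap on bilateral cases, and ask that patients "require single tooth replacement of the lateral incisor/canine region only on the affected cleft side". Objectives describe evaluation of one implant at the cleft site, and Operative Assessment refers to patients with one tooth missing there.

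The analysis paragraph in Results makes one provision for correlation: "The Cox model of analysis will be used to determine the shared frailty of dental implants in case of bilateral cleft cases". The same section names t, Wilcoxon and chi-square tests between 3 and 9 months, a binary logistic analysis of predictors, and a life table for survival. It mentions no cluster term for any of these.

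The precision basis is "With a type I error of 5%, confidence interval of 95%, and 8% margin of error", at an expected success of 95%, from which "a sample size of 28 dental implants was obtained".

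**The concern.** The frailty provision and the one-tooth wording pull in different directions. If each patient has one implant, a shared frailty has no clusters to work on. If a bilateral patient can have one implant per cleft side, two implants in the same mouth share host response, oral hygiene and possibly graft and operating session, so their outcomes are likely to be correlated. In that case 30 implants hold less information than 30 independent observations, and an interval for success or survival that ignores the pairing claims more precision than it has. The trial's main product is a success proportion with a stated margin, so that is where an error would show.

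**Working it through.** **1. The plan's own figure.** Inputs from Sample Size Calculation: p = 0.95, margin d = 0.08, 95% confidence.

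n = 1.96² × 0.95 × 0.05 / 0.08² = 28.5.

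The stated 28 agrees after rounding down, and 28 / 0.95 = 29.5 gives the stated 30. The calculation is the one-proportion formula for independent observations, with no design effect. Under independence the half-width is 1.96 × √(0.0475 / 28) = 8.07 points on 28 implants and 1.96 × √(0.0475 / 30) = 7.80 points on 30.

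**2. Effect of two-implant patients.** Let B be the number of patients who contribute two of the 30 implants. The mean cluster size weighted by implants is (4B + 30 − 2B) / 30 = 1 + 2B/30, so

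design effect (DEFF) = 1 + (2B/30) × ICC; effective n = 30 / DEFF; half-width = 1.96 × √(0.0475 × DEFF / 30).

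The coverage of a nominal 95% interval that ignores the pairing is approximately 2Φ(1.96 / √DEFF) − 1. The documents give neither B nor the ICC, so both are assumptions. All rows use 30 implants.

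| B | ICC | DEFF | Effective n | Half-width (points) | Coverage |
|---|---|---|---|---|---|
| 0 | any | 1.00 | 30.0 | 7.80 | 95.0% |
| 3 | 0.2 | 1.04 | 28.8 | 7.95 | 94.5% |
| 5 | 0.5 | 1.17 | 25.7 | 8.42 | 93.0% |
| 9 | 0.5 | 1.30 | 23.1 | 8.89 | 91.4% |
| 15 | 0.5 | 1.50 | 20.0 | 9.55 | 89.0% |

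The last row is a limit: it would mean that every patient has two implants and that no unilateral case is enrolled.

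**3. Can the Cox frailty term carry the load?** At 95% success, the expected number of failures is 30 × 0.05 = 1.5. Treating implants as independent, the chance of no failure at all is 0.95³⁰ = 0.21, and the chance of at most two is 0.81. A frailty variance cannot usefully be estimated from so few events. Even if it could, it would not correct the success proportion, the life table or the other tests.

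**4. Comparisons of 3 with 9 months.** If each implant is compared with itself, the relevant ICC is that of the within-implant change. This may be smaller than the ICC of the level, so the table above does not transfer to these tests.

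**The case against.** The strongest reply is that the harm is not established. Three places in the article point to one tooth or implant per patient, and a bilateral patient can be eligible with only one tooth missing. On that reading the design effect is 1 and the only fault is a superfluous frailty sentence. This stands as far as it goes: a reader might infer that the trial's intervals and P values are too optimistic as a fact, and the documents do not support that. They support it only if some patients contribute two implants. But on the one-implant reading the frailty sentence has no purpose, so the article still needs correcting.

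Second, the article condenses its methods and does not state the unit of analysis for the tests or the logistic model. A fuller plan may handle clustering. That is fair. Only the sample size demonstrably assumes independence. What can be said of the rest is that the article names a clustering device and attaches it to one model alone.

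Third, a reader might conclude that every other analysis is wrong and every interval too narrow. That goes too far. Clustering affects the variance of the success proportion and life table and does not in itself bias the estimates. For the between-time tests the relevant correlation is a different one, and an unpaired test could err in the opposite direction.

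Fourth, the size is assumed. With few pairs or a low ICC it is slight, and the larger figures need a majority of implants to be paired.

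**Conclusion.** The concern holds in conditional form. The frailty provision implies that some patients contribute two implants, while Objectives, Inclusion Criteria and Operative Assessment suggest one. The article must say which applies, and that conclusion needs no assumed ICC.

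If two are allowed and the ICC is positive, the stated precision and the intervals for success and survival are somewhat too narrow, and the Cox frailty term is no effective safeguard. In a moderate case (5 two-implant patients, ICC 0.5) the half-width grows by about 0.6 points (8.4 against 7.8). In a mild case (3 patients, ICC 0.2) it grows by about 0.15 points. With one implant per patient it does not change. No firm size can be given for the 3- versus 9-month comparisons.

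The point deserves correction before analysis but does not undermine the trial.

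**What to change.** State in Inclusion Criteria and in the analysis text whether a bilateral patient may contribute two implants, and align the one-tooth and one-implant wording with that rule.

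**If yes:**
- Report numbers of patients and implants separately, including how many patients have two.
- Give the success proportion with a Wilson interval that uses n / DEFF in place of n. Fix the ICC, with a range, in advance, because the data will hold too few failures to estimate it. A patient-level bootstrap is not suitable: it collapses to a point when there are no failures. GEE is also fragile with so few events.
- For continuous changes (bone level, ISQ, probing depth), use a patient random intercept or patient-level summaries.
- Add a sensitivity analysis with one implant per patient, for example the first placed. It also covers the life table and the binary findings.
- State that the 8% margin holds only if implants are independent.

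**If no:** delete the frailty model.

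The cost is slightly wider intervals and a little more analysis work. No additional implants are needed so long as the wider interval is accepted. Holding the 8% margin in the moderate case would instead take 28.5 × 1.167 = 33.3, so 34 implants, or 36 after 5% loss (34 / 0.95 = 35.8).

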### Objectives

The objectives of the study are to evaluate the placed single dental implant in the cleft region for clinical and radiological parameters 3 months after dental implant placement; evaluate the placed single dental implant in the cleft region for clinical and radiological parameters 9 months after dental implant placement (6 months after definitive prosthesis); and evaluate and compare the placed single dental implant in the cleft region for clinical and radiological parameters 3 months and 9 months after dental implant placement.

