## Methods

A single arm, prospective clinical trial evaluating the clinical and radiological success of immediately loaded dental implants in orofacial cleft patients will be conducted at the GSR Institute of CranioMaxillofacial & Facial Plastic Surgery, Hyderabad, Telangana, India. Ethical clearance for the clinical trial has been obtained from the Institutional Ethical Committees of the associated institutes. A summary of the methodology is presented in Figure 1.

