### Follow-Up

All patients will undergo 2 clinical follow ups, 3 months and 9 months after implant placement. At the first follow-up after a period of 3 months following immediate implant loading, the provisional prosthesis will be removed, and clinical and radiological parameters will be measured. Clinical parameters will include probing depth, bleeding on probing, suppuration, pain or tenderness in the implant area, and implant stability using ISQ values. The implant will then be loaded with a definitive prosthesis, and a CBCT will be recorded. A second follow-up will be performed after 6 months of definitive prosthesis placement (ie, a cumulative period of 9 months following implant placement), and all parameters will be assessed as stated previously. At the end of the treatment, all patients will be asked to complete a quality of life (QoL) assessment questionnaire to determine the patient’s perspective before and after dental implant treatment.

CBCT recordings will be done using a small sized field of view of approximately 50 mm in diameter, which has an effective dose of approximately 54µSv [18].

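### Chi-square tests are named for comparing 3- and 9-month findings, but the yes/no findings are two readings of the same implants and need a paired test

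*Protocol article*

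**What the plan says.** The Methods section describes "A single arm, prospective clinical trial evaluating the clinical and radiological success of immediately loaded dental implants in orofacial cleft patients", so there is no independent comparison group. The third aim listed under Objectives is to "compare the placed single dental implant in the cleft region for clinical and radiological parameters 3 months and 9 months after dental implant placement". Under Follow-Up, "All patients will undergo 2 clinical follow ups, 3 months and 9 months after implant placement", and at the second visit "all parameters will be assessed as stated previously".

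The same section lists what is measured: "Clinical parameters will include probing depth, bleeding on probing, suppuration, pain or tenderness in the implant area, and implant stability using ISQ values". Probing depth and ISQ are numeric. Bleeding, suppuration, and pain or tenderness are normally recorded as present or absent, although the article does not give the scale.

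The Results section then assigns the tests. After naming t tests, it states: "Wilcoxon tests, and chi-square tests will be utilized to determine statistical significance of clinical and radiological parameters assessed at 3 months and 9 months" after placement. The threshold is P<.05. The text names neither McNemar's test nor any other paired test for categorical data. The shared-frailty Cox model in the same section is tied to bilateral clefts and does not deal with repeat visits on one implant.

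**The concern.** Of the tests named, only chi-square suits a yes/no finding, so it is the one a reader would apply to bleeding, suppuration and pain. The ordinary test assumes independent observations. Here each implant contributes one reading at 3 months and one at 9 months, and an implant that bleeds at the first visit is more likely than others to bleed at the second.

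The article does not say how the table would be laid out. There are two obvious ways, and neither gives a valid test of change. What is at stake is the P value for the categorical findings in a stated objective. Depending on the layout, it would either be too large on average or answer another question altogether.

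**Working it through.** **Inputs from the protocol.** 30 implants; the same implants at 3 and 9 months; significance at P<.05 (two-sided assumed). The article gives no event rates, counts or within-implant correlations for these findings, so all such values below are assumptions. It also gives no figure for this comparison that could be reproduced. Its one calculation is the sample size, 1.96² × 0.95 × 0.05 / 0.08² = 28.51 (stated as 28, then 30 after losses). That is a precision calculation for a single proportion and does not use the 3- versus 9-month test.

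**Layout 1: stacked by visit (60 rows treated as independent).** With equal rates p at both visits, the stacked test takes the variance of the difference as 2p(1−p)/n. With within-implant correlation ρ the true variance is 2p(1−p)(1−ρ)/n. The large-sample size is therefore 2[1 − Φ(1.96/√(1−ρ))]:
- ρ = 0: 5%
- ρ = 0.3: 1.96/0.837 = 2.34, giving 1.9%
- ρ = 0.5: 1.96/0.707 = 2.77, giving 0.6%

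The exact size for n = 30 is the sum of multinomial probabilities over all possible tables that reject. At ρ = 0.5 it is 0.6% to 0.8% for rates between 10% and 50%, or about 0.7%. At ρ = 0 and a 30% rate it is 4.9%.

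Two illustrative tables:
- 9/30 falling to 3/30, with 6 implants changing one way and none the other. Pearson: 0.2² / (0.2 × 0.8 × 2/30) = 3.75, P = 0.053. Exact McNemar: 2 × 0.5⁶ = 0.031. Mid-P: 0.031 − 0.5⁶ = 0.016.
- 14/30 falling to 8/30, same split. Pearson P = 0.108; exact McNemar again 0.031.

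**Layout 2: 3-month result against 9-month result.** This tests whether the two visits are associated. Take 8 implants positive at both visits, 2 only at 3 months, 2 only at 9 months and 18 at neither, so 10/30 at each visit and no change. Pearson: 30 × (8×18 − 2×2)² / (10×20×10×20) = 14.7, P = 0.0001. Exact McNemar P = 1. With true rates of 30% at both visits and ρ = 0.5, this layout rejects 79% of the time.

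**Does a paired test gain power?** n = 30, two-sided 0.05, summed over all tables as above:

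| True rates | ρ | Stacked chi-square | Exact McNemar | Mid-P McNemar |
|---|---|---|---|---|
| 50% to 30% | 0.5 | 29% | 44% | 57% |
| 50% to 30% | 0.3 | 32% | 34% | 43% |
| 50% to 30% | 0 | 35% | 26% | 33% |
| 15% to 5% | 0.5 | 18% | 8% | 18% |
| 10% to 3% | 0.5 | 9% | 2% | 6% |

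The gain is clear only for common findings with substantial correlation. Exact McNemar is itself conservative: its size at ρ = 0.5 is 1.4% at a 30% rate and 0.1% at 10%. Mid-P reaches 3.3% and 0.6% in the same settings.

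**The case against.** The strongest reply is that the sentence lists families of tests and that McNemar's test has a chi-square statistic, so the authors may have meant it. That is possible. But nothing in the sentence says paired or matched, and someone following it literally would run an ordinary chi-square test. If McNemar was intended, naming it settles the matter.

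A second reply is that the stacked version is only conservative and so creates no false claims of change. This is true of that layout when the correlation is positive. It is not true of the cross-table.

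Some stronger readings are tempting but are not supported:
- A reader might infer that the t and Wilcoxon tests are wrong too. Both have paired versions under those names, and a condensed article can leave the variant to the fuller plan. A clarifying word would help, but its absence is not an error.
- A reader might infer that 3 versus 9 months is the trial's only comparison. The article also compares oral hygiene scores before grafting and before implant surgery, covers quality of life before and after treatment, and plans a logistic analysis of predictors.
- A reader might infer that chi-square generally misses real changes that McNemar would find. The table shows the opposite for exact McNemar at low correlation and for rare findings.

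**Conclusion.** The point stands as an error in a named analysis: an ordinary chi-square test does not fit a within-implant comparison of yes/no findings. Its size is about 0.7% instead of 5% if stacked at an assumed correlation of 0.5 (near nominal at 0). As a cross-table it rejects about 79% of the time with no change, at 30% positive on both visits and correlation 0.5. These figures rest on assumed rates and correlations, on 30 complete pairs, and on the findings being recorded as present or absent.

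The reach is limited to the categorical part of the third objective. A reader might infer that the trial's main result is compromised. It is not: the sample size, the consensus-based success rate and the life-table analysis do not use this test. Severity is moderate.

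**What to change.** In the statistical paragraph of the Results section, replace chi-square with McNemar's test for yes/no findings compared between 3 and 9 months. Mid-P is preferable, because the exact version is very conservative with 30 implants and for rare findings. Report the paired difference in proportions with a 95% CI, which will tell more than the P value where findings are rare. Where a patient contributes two implants, use a version that allows for clustering by patient. The same sentence can state that the t and Wilcoxon tests are applied to within-implant differences.

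The cost is one sentence. Enrolment, visits, data collection and sample size do not change, and the correction can be made before analysis.

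### At the protocol's own 95% success rate, about 1.5 failures in 30 implants cannot reliably support the planned logistic and Cox shared-frailty models of implant success

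*Protocol article*

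**What the plan says.** The Sample Size Calculation section of the protocol article rests on one planning rate: "A recent study showed a success rate of 95% for dental implant–based treatment in cleft patients". It continues: "With a type I error of 5%, confidence interval of 95%, and 8% margin of error, a sample size of 28 dental implants was obtained". Two implants are added for loss, giving 30. No effect size, power or event count for any model is given.

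The Results section then commits to two models without condition. One is logistic: "Binary logistic analysis will be done to compute the predictors of the outcome". The other is a survival model: "The Cox model of analysis will be used to determine the shared frailty of dental implants in case of bilateral cleft cases". Neither is called exploratory, and the same section sets a 5% significance threshold throughout. It also defines implant success by a consensus guideline and plans a life table for survival. The logistic outcome and its predictors are not named.

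The Follow-Up section sets the visits: "All patients will undergo 2 clinical follow ups, 3 months and 9 months after implant placement". The inclusion criteria require a single-tooth replacement on the cleft side and admit unilateral and bilateral clefts. The number of patients who will contribute two implants is not stated. The Limitations section concedes in general terms that the sample is small, but it does not tie this to either model.

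**The concern.** The sample size and the two models do not fit together. A sample chosen to put an interval around a 95% success rate contains very few failures by construction, and failures are what both models use. A logistic model of several predictors needs enough failures to spread across predictor levels. A shared-frailty variance needs patients with two implants, and needs failures among them.

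The practical risk is a table of odds ratios that rests on one or two failures and is tested at 5%. The Scope section expects the study to bring immediate loading into regular practice, so an apparent predictor could be read as guidance on patient selection even though the trial cannot support it.

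**Working it through.** **Inputs.** Success 95%, margin 8 percentage points, 95% confidence, 5% loss and 30 implants all come from Sample Size Calculation. Success of 95.8% to 98.6% and one-year survival of 98.4% come from the Discussion. The failure rates of 10% and 20%, the 15/15 predictor split and the number of two-implant patients are assumptions.

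**1. The plan's own figure.** n = 1.96² × 0.95 × 0.05 / 0.08² = 28.5. The article gives 28 (rounding up gives 29). After loss, 28 / 0.95 = 29.5, so 30. The stated size reproduces.

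**2. Expected failures, 30 × (1 − success rate).**

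| Success rate | Source | Expected failures |
|---|---|---|
| 98.6% | Discussion | 0.42 |
| 98.4% (survival) | Discussion | 0.48 |
| 95.8% | Discussion | 1.26 |
| 95% | Sample size | 1.5 |
| 90% | assumed | 3.0 |
| 80% | assumed | 6.0 |

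With 28 evaluable implants at 95%, the count is 1.4.

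**3. Distribution at 5% failure.** For Binomial(30, 0.05): P(0) = 0.95³⁰ = 0.215, P(≤1) = 0.554, P(≤2) = 0.812, P(≥5) = 0.016. With no failures, neither model can be fitted.

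**4. Logistic model, one predictor with no effect.** Ordinary maximum likelihood gives no finite odds ratio in these cases:
- *Binary, 15/15.* At least one group has no failures. The probability is 1 − (1 − 0.95¹⁵)² = 1 − (1 − 0.463)² = 0.71.
- *Continuous.* There are no failures, or all k failures lie at one end of the ranking. The probability is P(0) + Σ P(k) × 2/C(30,k). The terms are 0.215 + 0.339 × 2/30 + 0.259 × 2/435 + … = 0.215 + 0.023 + 0.001 = 0.24.

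| Failure rate | Binary 15/15 | Continuous |
|---|---|---|
| 5% | 0.71 | 0.24 |
| 10% (assumed) | 0.37 | 0.05 |
| 20% (assumed) | 0.07 | 0.002 |

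Fitting several predictors together makes separation more likely. Where an estimate is finite, it still rests on the counts in step 2.

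**5. Frailty variance.** Within-patient dependence shows only in patients with two implants. With m such patients, 5% failure and independence, P(at least one patient loses both) = 1 − (1 − 0.05²)^m. This is 0.0025 for m = 1 and 0.037 for m = 15, the most that 30 implants allow. Dependence raises it. If both implants always failed together, it would be 1 − 0.95^m, which is 0.05 for m = 1 and 0.54 for m = 15. The single-tooth criterion suggests that m may be well below 15.

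**The case against.** **The logistic outcome is not named.** The article also records yes/no findings such as bleeding, suppuration, tenderness and periapical pathology, and these could be commoner than failure. The full success criteria are not reproduced, so the threshold for non-success cannot be checked. This stands as a condition on the point. Implant success is still the natural reading, because it is the stated aim and the only binary outcome that the article defines as such.

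**The 5% is not specific to immediate loading.** It describes implant treatment in cleft patients generally, and failures may be more frequent here. This stands too, so a range is shown. Even an assumed 20% gives only 6 failures, and the other cited rates point lower.

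**A reader might infer that neither model can be estimated at all.** The figures do not support that. The 71% belongs to one assumed predictor layout, a continuous predictor such as stability at placement gives about 24%, and software will often return a number from one to three failures. The defect is unreliability.

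**A reader might also infer that two visits rule out a Cox model.** They do not. Cox models can handle tied or grouped times, and the article does not say that a loss between visits would go undated.

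**Prediction is not a stated objective.** No text says that predictors will guide selection, and they might be tested one at a time. This limits the harm but does not remove it, because both analyses are promised outright. Predictor lists can wait for a fuller plan, but a model commitment that conflicts with the article's own event rate is already fixed here.

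**Conclusion.** The point holds in a limited form. If the logistic outcome is implant success, the protocol's own rate gives about 1.5 failures in 30 implants (0.4 to 1.3 at the other cited rates, 3 to 6 at an assumed 10 to 20% failure). An ordinary logistic model of several predictors and a shared-frailty variance cannot then be reliably estimated. The chance of at most one failure is 55%, and the frailty term depends further on how many patients receive two implants, which is not stated. The general small-sample caveat under Limitations does not resolve this.

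The figures assume independent implants and, in step 4, a predictor with no effect. The point affects secondary analyses only. The success proportion and the life table remain sound aims, so it should be corrected but does not undermine the trial.

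**What to change.** Revise the Results section as follows.

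1. State that the success proportion with its confidence interval, and the planned life table, are the main analyses.
2. Replace the Cox shared-frailty model with a simple allowance for two-implant patients: a cluster-robust or patient-level bootstrap interval, or a sensitivity analysis with one implant per patient. Deleting the frailty model without a substitute would remove the only stated allowance for clustering, and a plain exact interval treats all implants as independent. If no failures occur, robust and bootstrap intervals collapse to zero width, so keep the one-implant-per-patient analysis with an exact interval for that case.
3. Name the logistic outcome. If it is implant success, use Firth-penalised logistic regression with one prespecified predictor at a time. Report intervals, label it exploratory, and do not select predictors on the 5% threshold. If there are no failures, omit it.
4. Optionally, relate the same few predictors to continuous outcomes already collected (implant stability and marginal bone level) by linear regression with patient-clustered errors. A patient random intercept would rely on the same few two-implant patients as the frailty term.

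The cost is analysis wording only, with no extra patients, visits or measurements. The downside is that the trial gives up any confirmatory claim about predictors of failure.
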